### Intervention Components

#### EMIs

The use of technology in this study allows participants to receive interventions in real time via the study smartphone in their natural environment. The study app on the phone has been configured to deploy specific interventions triggered by smoking status or the level of negative affect. Data are continuously collected via the sensors. Here, we describe the content of the EMIs, followed by the delivery procedure.

Active strategies include prompts to engage in mindfulness-based strategies and read motivational messages throughout the day. The majority of messages will be mindfulness strategies (n=76), which fall into the following topic areas: breath (eg, Turn your attention to your breathing. Notice where you feel your breathing most in your body), thoughts (eg, Observe any thoughts you are having right now. Watch them go by, just as leaves float down a stream of water—they just come and go), sensations (eg, Shift your attention to what you see around you. Be aware of the colors, shapes, textures, and shadows for the next several moments), acceptance/nonjudging (eg, Try to let go of labeling things as good or bad. Be present with what is happening and suspend judgment), and craving (eg, Whenever you have a craving to smoke, think of the craving like a wave in the ocean—it will come and go over time). Examples of motivational messages (n=40) are: “Quitting smoking may be uncomfortable at times, but it will get easier! Your cravings will become less frequent and less intense the longer you go without smoking. Don’t give up!” Figure 3 provides screenshots of the example strategies shown to the participants.

**Figure 3 figure3:**
[figure not shown]
Mindfulness strategies.

Strategy content is personalized in various ways to the participant. First, it is tailored to whether the participant is in the prequit or postquit portion of the study. For example, a prequit strategy would be “You’re doing a great job preparing to quit smoking!”, whereas a postquit strategy would be “Quitting is a process and takes time. Each hour you go without a cigarette is a step toward your freedom from nicotine. You’re doing great!” Second, strategies in the postquit phase are based on whether a participant has experienced a smoking lapse. An example of a lapse strategy is “Draw your attention to any thoughts you may be having about smoking. Remind yourself that you can get right back on track if you slipped off.” Third, participants rate how much they like a given strategy on a 5-point scale. If they rate it as one star (the lowest rating), they will not see that strategy again.

The day is separated into six 2-hour blocks for the delivery of EMIs. The decision point for randomization (ie, to send an active strategy or not) is based on smoking status and negative affect, both of which are being continuously monitored every minute while the equipment is being worn. For high negative affect, the decision to randomize is made as soon as a high negative affect event is detected within a 2-hour block and the participant is available. For lapse (ie, the detection of smoking), the decision to randomize is also made as soon as smoking is detected within the 2-hour block and the participant is available. Within a 2-hour block, this process is limited to one randomization occasion for high negative affect and one randomization occasion for lapse. For low negative affect, the decision point to randomize is randomly chosen at the start of the block, and if available when that time arrives, randomization occurs. If the participant is not available, another time is randomly chosen within that time block, and when that time arrives, assuming the participant is available, randomization occurs. This pattern is repeated until the end of the block. The process for randomization for no lapse is identical to the process of low negative affect, as previously described. Within a 2-hour block, randomization is limited to one occasion for low negative affect and one occasion for no lapse. In summary, up to 4 randomizations can occur within a 2-hour block (high negative affect, lapse, low negative affect, and no lapse). Moments will be randomized to receive a strategy or not in a 1:1 manner, and factors to ensure this 1:1 randomization will be included in the algorithm (ie, inclusion of historical data of what has already been triggered that day). Figure 4 shows the process of randomization based on the detection of high negative affect (low negative affect, lapse, and no lapse processes are not included in the figure for simplicity purposes, but their procedures mimic what is shown for high negative affect).

**Figure 4 figure4:**
[figure not shown]
Randomization process based on the detection of high negative affect (low negative affect, lapse, and no lapse are not represented here for simplicity purposes). R: randomization.

When considering low/high negative affect and lapse/no-lapse occasions, participants can receive up to 2 active strategies within a block (ie, they receive a mindfulness strategy or motivational message). Thus, participants can receive up to 12 active strategies per day. Other conditions are also considered for the delivery of the strategies. These include time since last EMA being at least 15 min, time since last EMI being at least 30 min, good quality data detected via sensors, no driving, phone battery level at least 10%, and no engagement in physical activity. Given the above conditions for the delivery of EMIs, we do not anticipate individuals receiving more than 6 per day, and they may even receive fewer than 6. For instance, if someone does not lapse, then no strategies are sent for that purpose. AutoSense will not send messages when it detects driving, so no messages are sent during those times.

When active strategies are sent to participants, they will receive a notification on the phone, allowing them to know that a strategy is available. They will have the option of accepting it, delaying it for 5 min, or canceling it altogether. When participants agree, they will have the option of receiving a new strategy if they do not like the first one that appears on the phone. Participants will then let the app know whether they completed the strategy, and if they indicate *yes*, they will be asked to rate how much they liked the strategy on a scale of 1 to 5 stars. If they select 1 star, then this strategy will not be shown again to the participant.

#### On-Demand Mindfulness Content

In addition to the strategies and surveys that will be sent to a participant’s phone, participants will also have the opportunity to practice strategies on their own (ie, user-initiated). There is a mindfulness strategy button within the app that can be clicked at any time by the participant to receive a strategy. Although participants will be choosing to engage in a strategy as opposed to being sent one, the process will be similar to that described above (eg, rating the strategy). Participants will be informed at visit 1 that they can click on this button at any time. The phone also has a Mindfulness Frequently Asked Questions (FAQ) button that participants can click at any time to learn more about mindfulness. This feature contains 13 common questions about mindfulness, such as *What is mindfulness?* and *How does being aware of my thoughts relate to me quitting smoking?*

#### In-Person Counseling

During visits 1-4, participants will receive brief counseling (20-30 min) at the end of their sessions. Counseling will be consistent with the Treating Tobacco Dependence Guidelines [67] and will also incorporate a brief mindfulness component. At visit 1, participants will be provided with the National Cancer Institute’s Clearing the Air Booklet [68] as well as instructions on how to use the nicotine patch. They will also be given a single-page handout on mindfulness (eg, definition of mindfulness and why we suggest using mindfulness to help quit smoking). In visits 1-3, participants will listen to a 10-minute audio recording of a mindfulness meditation. At visits 1 (prequit) and 3 (postquit), participants will listen to a recording on urge surfing; at visit 2 (quit day), an audio recording of guided breath meditation will be used. Following these meditations, the counselor will ask questions such as *What did you notice while listening to the recording?* and *How do you think what you just heard is related to quitting smoking?*

#### NRT

Participants will receive 6 weeks’ worth of 14 mg or 21 mg nicotine patches throughout the duration of the study. At visit 1, participants will receive patches and instructions on how to use them. Participants will be instructed to begin wearing the patch at the beginning of the day of their visit 2 (quit day). If a participant smokes 10 or less cigarettes per day, they will be given 14 mg patches. If the participant smokes more than 10 cigarettes per day, they will be given 21 mg patches. At visit 5 (follow-up), participants will receive 2 weeks’ worth of the dosage that they have been using for the last 28 days (totaling 6 weeks of patches) and will be given additional guidance on how to continue the patch regimen. At the end of the last visit, participants will also be given recommendations on how to obtain nicotine patches from community sources as well as additional quit smoking and counseling referrals, if needed.

### Analyses

#### Feasibility Outcomes

Our measures of feasibility and associated benchmarks of success include the following: retention (≥75% through follow-up), adherence (eg, expect ≥70% of participants to wear the equipment the majority of the 14 days; of those who wore the equipment the majority of the 14 days, ≥70% completion of EMAs; ≥60% of strategies completed), and a score of 68 or higher on the System Usability Scale. Acceptability will be primarily driven by scores on the Client Satisfaction Questionnaire (≥3), followed by responses to the mindfulness strategies.

#### Exploratory Outcomes: Sensor-Based Collection of Negative Affect, Self-Regulatory Capacity, and Smoking Status

Wearable sensors are configured to detect negative affect, self-regulatory capacity, and smoking status, to deliver and ultimately collect outcome data on relevant intervention content to the study phone. The experience of negative affect is detected through a machine learning model applied to continuous sensor-based measurements based on electrocardiogram (ECG) and respiration data [62]. Respiration data are measured via inductive plethysmography (RIP), which is the contraction of the chest and abdominal wall, as collected by the chest band [62]. ECGs are measured via 2 electrodes connected to a chest box unit. Probability of experiencing negative affect is derived from these measures, which will be used as our indicator of negative affect; additional detail can be found in the study by Hovsepian et al [62]. Self-regulatory capacity will be captured via heart rate variability, which is also captured by the ECG data.

Smoking episodes are detected via the *puffMarker* model, a machine learning algorithm that uses respiration data to detect deep inhalation and long exhalation and wrist movement patterns to detect hand-to-mouth gestures [63]. Inhalation and exhalation data are collected via RIP sensors, whereas specific wrist movements indicative of smoking are collected by wrist bands with a 3-axis accelerometer and a 3-axis gyroscope [63]. All of the data collected by the sensors are continuously measured and wirelessly streamed to the study phones and then sent to the cloud for analysis [63].

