#### Ecological Momentary Assessments/Surveys on Phone

Ecological momentary assessments (EMAs) will be delivered randomly within prespecified time blocks as well as after a subset of EMIs during the 2-week period. All methodologies for randomly allocating EMAs were preprogrammed using a random number generator function. Randomization also considers what has already been sent historically during that day and is based on certain conditions, as described below. Random EMAs are delivered within 3- to 4-hour blocks throughout the day. Thus, participants will receive no more than 1 survey per 4-hour block to limit the participant burden (up to 3 random EMAs per day). The system is also configured to deploy EMAs after EMIs (described below), 50% of the time. For an EMA to be delivered, certain conditions must be met: time since the last delivered EMI followed by EMA must be more than 15 min, data quality must be classified as good (ie, sensors are attached correctly to the user and the sensors are communicating correctly with the smartphone; red, yellow, and green indicators will be visible to participants so they can fix the equipment if needed. This allows for the sensor data collected in the vicinity of the moment of EMA to be available for analysis), and the participant cannot be driving or engaging in physical activity (to increase the likelihood of responding) [66].

When it is time to take a survey, participants will receive a notification on their phone. Participants will have the option of completing it, delaying it for 5 min, or canceling it altogether. EMAs take an average of 3-5 minutes to complete and assess the following broad areas: mindfulness, affect, motivation, urge to smoke, expectancies, self-efficacy, smoking behaviors, patch use, social setting, alcohol use, discrimination, stressors, and general emotional support. An item assessing whether participants have been using the mindfulness strategies, without the aid of their smartphone, will also be presented.

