#### Analytic Plan

Descriptive statistics (eg, means and percentages) will be derived for feasibility and acceptability outcomes. Given that this is a feasibility study, sensor-driven analyses will be exploratory with the goal of providing preliminary results. The unit of analysis is the pre/postengagement data pairs comparing the average negative affect, self-regulatory capacity, and lapse counts within a prespecified time frame (eg, negative affect and self-regulatory capacity in the 30 minutes before and after randomization and lapse status in the time period between randomization of EMIs). These data will be analyzed using a generalized linear mixed model with proper adjustment for the within-subject correlation. The model can also include indicators for the category of mindfulness strategy. Each variable pair (negative affect, self-regulatory capacity, and smoking) will be analyzed separately in a pre/postengagement comparison to determine whether the mindfulness intervention creates any changes in these variables when compared with receiving no strategy at all. Examples of potential time-invariant covariates that will be included in the model are gender, age, education level, baseline trait mindfulness, and nicotine dependence. Time-varying covariates to be considered in the models include smoking status and use of the *on-demand* mindfulness content. Given that MRTs require unique considerations regarding data analysis (eg, participant availability and changes in the use of the intervention over time), we will incorporate the most recent recommendations in the literature when examining the data [69,70].

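### The sensor-derived negative-affect score uses respiration as an input and its example post window includes strategy practice, so a lower score after a strategy need not mean lower negative affect

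*Protocol article*

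**What the plan says.** All references are to the protocol article.

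- **Outcome.** Under Exploratory Outcomes, negative affect is "detected through a machine learning model applied to continuous sensor-based measurements based on electrocardiogram (ECG) and respiration data". The same section continues: "Probability of experiencing negative affect is derived from these measures, which will be used as our indicator of negative affect". For the second outcome it says: "Self-regulatory capacity will be captured via heart rate variability, which is also captured by the ECG data".
- **Intervention.** Under EMIs: "The majority of messages will be mindfulness strategies (n=76), which fall into the following topic areas". Breath is one of the five topics, and its example reads: "Turn your attention to your breathing. Notice where you feel your breathing most in your body". There are also 40 motivational messages, which count as active strategies.
- **Contrast.** The Analytic Plan compares pre/post pairs at strategy moments with those at no-strategy moments. Its example of a time frame is "negative affect and self-regulatory capacity in the 30 minutes before and after randomization". It describes no exclusion of practice time. Indicators for strategy category may be added but are not required.
- **Self-report.** Under Ecological Momentary Assessments: "EMAs take an average of 3-5 minutes to complete and assess the following broad areas: mindfulness, affect". The Analytic Plan names only sensor measures for this contrast.
- **Status.** The Analytic Plan calls the sensor analyses exploratory and their results preliminary.

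**The concern.** At a strategy moment the participant may be asked to attend to breathing; at a no-strategy moment nothing is asked. Respiration feeds the model that produces the negative-affect score, and the post window opens at randomization, so it takes in the practice itself. If practice alters breathing for a few minutes, the score can move at strategy moments only, with affect unchanged. The comparison would then detect a real difference in the score, and the report could present it as lower negative affect.

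What is at stake is interpretation. Study Aims hypothesizes lower negative affect, and the Discussion expects the findings to show how mindfulness acts on underlying mechanisms and recommends a large randomized trial as a next step. A category comparison would be the most exposed, since the breath topic could appear to be the effective one.

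**Working it through.** The article gives no significance level, power or effect size for this contrast, so there is no figure of its own to reproduce. The check asks how often the contrast would reject if affect did not change but practice shifted the score.

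**Inputs from the article**
- 24 participants, 14 days, 1:1 randomization of moments.
- 76 mindfulness strategies and 40 motivational messages: mindfulness share 76/116 = 0.655.
- Completion 0.60, the stated benchmark for strategies completed.
- Post window 30 minutes.

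**Assumptions not in the article**
- 6 randomizations a day, so 24 × 14 × 6 = 2016 randomizations and 1008 strategy moments.
- Five equal topics: breath share 0.655/5 = 0.131.
- Practice of 3-5 minutes, shifting the per-minute score by 0.5-1 SD.
- SD of the analysed 30-minute value equal to 0.6 of the per-minute SD.
- Two-sided 5% test.

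**Formulas**
- Bias = share × 0.60 × (practice minutes/30) × shift.
- SE, strategy versus none = 0.6 × √(2/1008) = 0.0267.
- Rejection = Φ(z − 1.96) + Φ(−z − 1.96), with z = bias/SE.

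**Only breath strategies act, overall contrast**
- Low: 0.131 × 0.60 × 3/30 × 0.5 = 0.0039; z = 0.15; rejection 5%.
- High: 0.131 × 0.60 × 5/30 × 1 = 0.0131; z = 0.49; rejection 8%.

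**All mindfulness content acts, overall contrast**
- Low: 0.655 × 0.60 × 3/30 × 0.5 = 0.0197; z = 0.74; rejection 11%.
- High: 0.655 × 0.60 × 5/30 × 1 = 0.0655; z = 2.45; rejection 69%.

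**Breath category versus none (optional term)**
- Breath moments: 1008 × 0.131 = 132. SE = 0.6 × √(1/132 + 1/1008) = 0.0555.
- Low: 0.60 × 3/30 × 0.5 = 0.030; z = 0.54; rejection 8%.
- High: 0.60 × 5/30 × 1 = 0.100; z = 1.80; rejection 44%.

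**Sensitivity to the noise assumption.** The unit of analysis is a pre/post pair. If the pre and post windows are uncorrelated, the SD of the change is larger by √2 (0.6 × √2 = 0.85). The ranges become 5-6% (breath only), 8-41% (all mindfulness content) and 7-25% (breath category). With a pre/post correlation of 0.5 the SD of the change is 0.6 again, and the ranges are as above.

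**A second set of assumptions.** With 6 active strategies a day (2016 strategy moments), SE = √(2/2016) in SD units of the 30-minute change, and a 1 SD shift on that scale, the breath-only overall contrast rejects in 5.7% (3 minutes), 7.0% (5 minutes) and 13.1% (10 minutes). With no shift it rejects in 5.0%.

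**The case against.** The case against is substantial, and most of it stands.

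- **Altered breathing is an inference.** The breath example asks for attention to breathing, not for a different rate or depth, and nothing in the article says that a strategy changes respiration apart from affect. A reader might infer that the strategies change the outcome directly; the article supports only that they may.
- **Heart rate variability.** A reader might extend the argument to self-regulatory capacity. As the article defines it, that measure comes from ECG alone, and unchanged affect is not its null hypothesis. What carries over is only that its post window also contains the practice.
- **The large figures.** These need either every mindfulness topic to alter breathing, which the article does not support, or the category contrast, which is optional. The shift size, practice time, noise and equal topics are all assumed.
- **Validity of the test.** A reader might infer that the planned test is invalid. It is valid for the sensor score, which the article openly calls an indicator.
- **Exploratory status.** The window is given only as an example, the analyses are exploratory, and the Discussion says that the small sample limits conclusions. A full analysis plan may settle the window and the use of self-report. This lowers the priority.

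The guided breath meditation at visit 2 is no support for the concern either: every participant hears it, so it does not separate strategy from no-strategy moments within a person.

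What remains is that the score shares an input with what one topic targets, the example window covers the practice, and the stated contrast has no affect measure independent of the sensors.

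**Conclusion.** The point holds as a caution on interpretation. A lower negative-affect score in the 30 minutes after a strategy may reflect changed breathing during practice, changed affect, or both, and the contrast as described cannot tell them apart.

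The size cannot be fixed from the article. If only breath strategies act, the planned overall contrast stays near nominal, at about 5-8% with 6 randomizations a day. Material excess is confined to the optional category contrast (8-44%) or to the case in which most mindfulness content alters breathing (11-69% if all of it does). These figures rest on the assumptions listed in the working and show what is possible, not what is expected. Low priority.

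**What to change.** 1. Keep 0-30 minutes after randomization as the main analysis for both outcomes.
2. Add a prespecified sensitivity analysis that drops the practice minutes. Apply the same clock window at no-strategy moments, and define it from randomization rather than from each completion time, which no-strategy moments lack. The cutoff should allow for the 5-minute delay option described under EMIs.
3. Add self-reported affect as a companion outcome, using random EMAs within a stated lag after randomization at both kinds of moment. Allow for the 15-minute spacing rules between EMIs and EMAs, which could otherwise make survey timing differ between strategy and no-strategy moments. Do not rely on EMAs sent after EMIs until it is settled whether they also follow no-strategy randomizations; the article does not say.
4. Report the primary sensor result as a change in the sensor-derived score, and call it a change in affect only with the self-report result shown beside it.

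The cost is a little more analysis work. No new data are needed, and the article describes data management as ongoing. The EMA comparison will be less precise, with at most 3 random EMAs a day, and the shortened window cannot show an effect confined to the practice minutes, which is why it should not replace the main analysis.
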